### Sample size calculations

In our pilot study [25] evaluating the effect of acupuncture on insulin sensitivity in PCOS women with IR, HOMA-IR reduced significantly after 3 months of acupuncture treatment when an interim analysis was performed and changed from (4.3 ± 2.5) vs. (3.7 ± 2.1). HOMA-IR ≥2.14 was considered to be abnormal. We anticipate that the HOMA-IR after 4 months of true acupuncture treatment will decrease 25%, and sham acupuncture will be decreased 5% as it is well known that sham is not an inert procedure. Therefore, the difference is 20%, with two-sided α assigned to be 5% and β 20% at the upper limit, respectively, at which the power is 80% and the rate of attrition estimated to be 20%. Thus, the sample size has been inflated from 95 to 114 per group, totaling 342 cases for the three arms. The sample size was calculated using the software statistics toolkit supported by the Department of Obstetrics and Gynecology of the Chinese University of Hong Kong (http://www.obg.cuhk.edu.hk/ResearchSupport/StatTools/index.php).

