### Statistical analysis strategy

The Kolmogorov-Smirnov test will be used to test the normal distribution of continuous variables. Continuous variables will be presented by mean ± standard deviation if they are normally distributed or by median with interquartile range if they are not normally distributed. Both per protocol (PP) analysis and intention-to-treat analysis (ITT) will be used to determine the robustness of the evidence. Analysis of variance (ANOVA) with Bonferroni corrections will be used for comparing the differences between groups of continuous data in accordance with a normal distribution or Kruskal-Wallis test for non-normal distribution data when appropriate; χ^2^ tests will be used for comparison of dichotomous data. For the primary outcome, analysis of covariance (ANCOVA) (accompanying LSMEAN and 95% CI) will be used. ANOVA will be used to calculate the changes from baseline to after treatment and follow-up, respectively, and it will also be used to compare the differences between treatment arms with respect to the primary outcome, HOMA-IR. Effect of continuous data will be reported by both *P*-value and mean difference with 95% confidence interval and categorical data by *P*-value and relative risk (RR) and risk difference (RD) with 95% confidence interval; the number needed to treat (NNT) will be calculated if there is statistical significance between groups. All statistical analyses of the data will be performed by using SPSS software version 21.0 (SPSS Inc., Chicago, IL, USA).

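### The primary analysis is not fixed: the primary outcome is assigned to ANCOVA and then also to ANOVA, a normality-test rule could divert it to Kruskal-Wallis, and no result is named as confirmatory

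*Protocol article*

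**What the plan says.** All the analysis rules stand in one paragraph of the protocol article, Statistical analysis strategy.

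- A general gate for continuous data: "The Kolmogorov-Smirnov test will be used to test the normal distribution of continuous variables". Normal data then go to ANOVA with Bonferroni corrections; otherwise the plan names the "Kruskal-Wallis test for non-normal distribution data when appropriate".
- A specific rule: "For the primary outcome, analysis of covariance (ANCOVA) (accompanying LSMEAN and 95% CI) will be used". No covariate is named.
- The next sentence uses ANOVA for changes from baseline to the end of treatment and to follow-up, and adds that "it will also be used to compare the differences between treatment arms with respect to the primary outcome, HOMA-IR".

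The Primary outcome section defines the outcome as change in HOMA-IR. The paragraph promises a mean difference with 95% confidence interval for continuous data. No sentence ranks the tests or calls one of them primary.

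**The concern.** Two adjacent sentences give the same between-arm comparison to two different models, and a third rule may replace both after looking at the data. This is a conflict between stated rules, not a detail left for a later document.

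Three things are at stake:

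- **Type I error.** If the reported test can be picked after the results are seen, the 5% level no longer holds.
- **Power.** ANOVA on change uses baseline only by subtracting it. ANOVA on post-treatment values does not use it at all. Neither adjusts for baseline HOMA-IR as a covariate, so both can be less precise than ANCOVA on the same data.
- **The estimate.** Kruskal-Wallis yields neither the least-squares means nor the mean difference with confidence interval that the plan promises.

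**Working it through.** **1. Inputs.** From Sample size calculations: pilot HOMA-IR 4.3 (SD 2.5) before and 3.7 (SD 2.1) after treatment; planned falls of 25% (true) and 5% (sham); "with two-sided α assigned to be 5% and β 20% at the upper limit"; 95 per group, inflated to 114. From Inclusion Criteria: HOMA-IR of at least 2.14. The article gives no baseline-to-follow-up correlation, so r is assumed and varied.

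**2. The plan's own figure.** Difference: 4.3 × (0.25 − 0.05) = 0.86. With SD 2.1:

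n = 2 × (1.960 + 0.842)² × 2.1² / 0.86² ≈ 94 per arm.

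The t-based version gives 94.6, that is 95, and 95 × 1.2 = 114. SD 2.5 would give 133. The stated number is therefore reproduced by an unadjusted two-arm comparison of post-treatment values.

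**3. Closed-form power at 95 per arm, two-sided 5%.**

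Power ≈ Φ(0.86 / (SD × √(2/95)) − 1.96), with SD equal to:

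- post-treatment values: 2.1
- change: √(2.5² + 2.1² − 2r × 2.5 × 2.1)
- ANCOVA on baseline: 2.1 × √(1 − r²)

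At r = 0.5 the change SD is √(6.25 + 4.41 − 5.25) = 2.33 and the ANCOVA SD is 2.1 × √0.75 = 1.82.

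| r | ANCOVA | ANOVA on change | ANOVA on post values |
|---|---|---|---|
| 0.3 | 84% | 58% | 81% |
| 0.5 | 90% | 72% | 81% |
| 0.7 | 98% | 90% | 81% |
| 0.8 | 99.7% | 98% | 81% |

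**4. Is HOMA-IR skewed?** The entry floor lies (4.3 − 2.14)/2.5 = 0.86 SD below the pilot mean. A normal distribution would put about 19% of patients below a floor that admits none. Right skew of the values is a fair inference, although the article does not state it.

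**5. Simulation with skew.** Assumed lognormal with mean 4.3 and SD 2.5, so log-scale SD = √ln(1 + (2.5/4.3)²) = 0.54; follow-up ratios 0.75 and 0.95; 95 per arm; pairwise tests at two-sided 5%.

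| Log-scale r | Raw ANCOVA | ANOVA on change | ANCOVA and change ANOVA disagree |
|---|---|---|---|
| 0.3 | 82% | 56% | 31% |
| 0.5 | 88% | 70% | 20% |
| 0.7 | 97% | 87% | 11% |
| 0.8 | 99% | 97% | 3% |

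ANOVA on post-treatment values stays at about 80% throughout. Independent runs of the same model differ by a few points.

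**6. Type I error.** With no treatment difference, each test alone holds about 5%. The chance that at least one of ANCOVA, change ANOVA and the rank test on change is significant is about 7-9% per comparison. This is the worst case, in which the favourable result is the one reported.

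**The case against.** The strongest reply is that the sentence opening with the primary outcome is specific, comes after the general rule, and names a sound model. On that reading ANCOVA governs, ANOVA is supplementary, and Kruskal-Wallis, qualified by its closing words, never reaches the primary outcome. This weakens the Kruskal-Wallis route, which is only a possible one. It does not settle ANCOVA against ANOVA: the ANOVA sentence is equally specific to the primary outcome and comes last.

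A reader might infer more than the document supports:

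- **That the ANOVA and Kruskal-Wallis routes ignore baseline.** The primary outcome is a change and ANOVA is tied to changes from baseline, so baseline enters by subtraction. Only a test of post-treatment values leaves it out.
- **That a large loss of power is established.** In closed form the loss for change scores against ANCOVA runs from about 26 points at r = 0.3 to 2 at r = 0.8, and r is unknown. ANOVA on post-treatment values keeps roughly the planned 80%, because the sample size reproduces as that comparison. Rank tests on skewed data do better than the matching raw-scale ANOVA.
- **That the normality test will almost surely reject.** That holds for HOMA-IR values tested with the Lilliefors correction (about 97% under the lognormal model). The primary outcome is change, to which the entry floor does not apply. For change, rejection is about 64-83% with Lilliefors in the true acupuncture arm and somewhat lower in the sham arm (48-72%). With the uncorrected Kolmogorov-Smirnov test it is about 10-28% and 6-15% respectively. The route is hard to predict, not predetermined.
- **That analysing the raw scale is an error.** Raw-scale ANCOVA had 82-99% power here. The log scale is a preference with good reasons.

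**Conclusion.** The point holds in this form: the article names two models for one primary comparison, leaves the ANCOVA covariate open, sets a data-dependent rule beside them, and ranks none of them. That much is read directly from the text and needs no assumption.

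The consequences rest on an assumed lognormal model, 95 evaluable patients per arm and log-scale correlation 0.3 to 0.8. Change-score ANOVA falls short of the planned 80% at correlation 0.5 or less and exceeds it at 0.7 or more. The disagreement rate and the 7-9% error rate show what an open choice could cost; they do not predict that the choice would be abused. The defect deserves correction because it concerns the trial's confirmatory test.

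**What to change.** State one confirmatory analysis: ANCOVA of HOMA-IR at the 4-month visit on treatment arm, with baseline HOMA-IR and the site factor used in stratification as covariates. The log scale is preferable, since the effect was planned as a percentage fall and the entry floor suggests skewed values; results would then be ratios of geometric means with 95% confidence intervals.

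Delete the sentence that gives the primary between-arm comparison to ANOVA. Say that the normality-test rule does not apply to the primary outcome. List ANOVA and Kruskal-Wallis as sensitivity analyses.

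The cost is wording only. Baseline OGTT and insulin tests are already scheduled in Table 3, and no added patients or visits are needed. The one small downside is that a log-scale effect is reported as a ratio rather than in HOMA-IR units. Trial status reports 114 of 342 randomized at the end of December 2016; the change should be dated before unblinding.

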#### Secondary outcomes

Improvement rate of HOMA-IR.HOMA-β: Islet β-cell function will be evaluated by the formula (20 × fasting insulin (mU/ml) / (fasting plasma glucose (mmol/l) − 3.5)) [42] and by the C-peptide index (CPI) Fasting C-peptide (nmol/l)/f-glucose (mmol/l) × 100 [43].The insulin response to glucose will be assessed by calculating the area under the curve during the OGTT and Ins performance for glucose (AUCglu) and insulin (AUCins) using the trapezoidal rule [44].Frequency of menstrual cycles and ovulation.Body composition: weight, BMI, waist-to-hip circumference, and FG and acne lesion counts.Metabolic profile: glucose and insulin concentrations, C-peptide, HbA1c, TC, TG, HDL-C and LDL-C, and ApoA1 and ApoB.Hormonal profile: FSH, LH, T, and SHBG.Questionnaires: SF-36, ChiQOL, sleeping questionnaires, IPAQ,QEWP, PCOS-QOL, Zung SAS, Zung SDS questionnaires, and the quantization table of TCM syndromes about PCOS will be used to assess the quality of life and sleep and the emotional state and to measure the moderate physical activity.Side effect profile.Expectation and credibility of treatment.

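### For secondary continuous outcomes that fail the normality check, the P-value comes from a rank test but the reported effect is a mean difference with its interval, so the two can disagree

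*Protocol article*

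**What the plan says.** The section Statistical analysis strategy of the protocol article sets up two routes for continuous variables and then one reporting rule.

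- **Switch:** "The Kolmogorov-Smirnov test will be used to test the normal distribution of continuous variables".
- **Summary on the non-normal route:** "by median with interquartile range if they are not normally distributed".
- **Test on the non-normal route:** "Kruskal-Wallis test for non-normal distribution data when appropriate".
- **Reporting, with no exception for that route:** "Effect of continuous data will be reported by both *P*-value and mean difference with 95% confidence interval". The effect measure on both routes is thus a "mean difference with 95% confidence interval".

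The section names no transformation, median difference or rank-based effect estimate. The primary outcome has a sentence of its own: "For the primary outcome, analysis of covariance (ANCOVA) (accompanying LSMEAN and 95% CI) will be used".

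The outcomes most likely to take the rank route are under Secondary outcomes. One entry reads "Metabolic profile: glucose and insulin concentrations, C-peptide, HbA1c, TC, TG, HDL-C and LDL-C, and ApoA1 and ApoB"; others include HOMA-β, the areas under the glucose and insulin curves, and acne lesion counts.

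**The concern.** A rank test does not test a difference in means. The interval for a mean difference on the original scale depends heavily on the upper tail, and that tail is what sends a variable to the rank test. Following the rule, one table row could show P < 0.05 beside a 95% interval that includes zero, or the reverse. The row would also carry medians that correspond to neither. A reader would not know which quantity is the finding. What is at stake is how clearly the skewed secondary outcomes can be read, not the trial's main conclusion.

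**Working it through.** The plan gives no figure for this point, so the check has two parts: do the sentences collide, and how often would it show?

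**1. Do the sentences collide?** Take an outcome that fails the normality test. Its summary is a median, its P-value is rank-based, and its effect is a mean difference. The words that soften the choice of Kruskal-Wallis apply to the test and not to the reporting sentence. The collision follows from the text. That the mean difference is on the raw scale is an inference from the absence of any named transformation.

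**2. Would such outcomes reach the rank route?** The only spread in the document is the pilot HOMA-IR under Sample size calculations, 4.3 ± 2.5 and 3.7 ± 2.1. If log-normal, log-SD = √ln(1 + (SD/mean)²):

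- √ln(1 + (2.5/4.3)²) = √ln 1.338 = 0.54
- √ln(1 + (2.1/3.7)²) = √ln 1.322 = 0.53

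For log-normal samples of 91, a Kolmogorov-Smirnov test with the Lilliefors correction rejected normality in 92% (log-SD 0.5), 98% (0.6) and 100% (0.8) of simulated samples. Outcomes of this shape would usually take the rank route.

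**3. How often do P-value and interval disagree?** Inputs:

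- 91 per arm, from 114 × (1 − 0.20) = 91.2 (Sample size calculations).
- Two-sided 5% level (same section).
- Log-SD 0.5, 0.6 and 0.8, and true ratios of 0.85 and 0.80. These are assumptions; the document gives no spread or effect for insulin, triglycerides or AUCins.
- Mann-Whitney as the pairwise rank test, because the plan names none, and a Welch interval for the mean difference. No baseline adjustment. 3,000 trials per setting.

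Share of trials in which rank P < 0.05 and exclusion of zero by the 95% interval do not agree:

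| log-SD | ratio 0.85 | ratio 0.80 |
|---|---|---|
| 0.5 | 14.5% | 9.1% |
| 0.6 | 15.2% | 14.1% |
| 0.8 | 16.3% | 19.9% |

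The simulation error is small: at 14%, √(0.14 × 0.86 / 3000) = 0.6 points. A significant rank test beside an interval that includes zero makes up 6 to 15% of all trials; the rest is the reverse.

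A second set with 95 per arm (4,000 runs) gives the same order:

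- Planned effect (25% against 5% decrease), CV 0.58 as in the pilot: 6.9 + 3.0 = 9.9%.
- Half that effect, same CV: 7.2 + 4.6 = 11.8%.
- Planned effect, CV 1.0: 14.3 + 5.9 = 20.2%.

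**4. How much of this is due to skew?** Two different tests always disagree sometimes near the threshold. With the rank test and the Welch test both applied to the logged data, which are exactly normal, they still disagree in about 5 to 7% of trials (4.5 to 7.8% across repeat runs). The excess is lowest at log-SD 0.5, ratio 0.80 (9.1 − 4.5 = 4.6, about 5 points) and highest at log-SD 0.8, ratio 0.80 (19.9 − 7 = about 13, or 14 with simulation error). In five of the six settings it is about 5 to 9 points.

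**The case against.** **The article is a summary.** The reporting sentence is general, and the effect measure for rank-tested outcomes is a detail that an analysis plan may settle. This has force: an unseen plan may already repair the matter. But the article is not silent. It states a rule for all continuous data, having just created a route on which that rule does not match the test.

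**Both quantities are valid.** With about 91 per arm, a mean difference has an approximately correct interval even for skewed data, and a rank test is sound for what it tests. That stands. The defect is in the pairing. Preferring a geometric-mean ratio is partly a choice of estimand.

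**The spread is assumed.** The pilot figures correspond to a log-SD near 0.54, close to the lower end of the range. The 20% figure comes from the upper end. That also stands.

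**Stronger readings that a reader might infer, and that are not supported:**

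- *That the primary result is exposed.* HOMA-IR has its own mean-based model, with interval and test from the same analysis.
- *That skew causes the whole 9 to 20%.* Part of it would occur with normal data.
- *That mean and median differences will often point in opposite directions in a way that matters.* Runs with opposite signs and either test significant were at most about 0.2%.
- *That the rule costs much power.* The plan's P-value comes from the rank test. For a 20% reduction at log-SD 0.6 that has about 68% power, against about 71% for a log-scale test.
- *That disagreement could be the rule.* It reached 73% (equal means) or 62% (equal medians) only when the arms were given very different skew (CV 0.4 against 1.0), for which the document gives no basis.

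**Conclusion.** The point holds in a limited form and is one to consider. For secondary continuous outcomes that fail the normality check, the reporting rule puts a rank-test P-value beside a mean-difference interval from a different analysis. On the assumptions above, the two disagree on significance in about 9 to 20% of trials per outcome, of which skew accounts for roughly 5 to 14 points. This rests on log-normal outcomes with log-SD 0.5 to 0.8, reductions of 15 to 20%, a pairwise rank test in place of the three-arm Kruskal-Wallis test, and the mean difference being on the original scale. The primary HOMA-IR ANCOVA and the sample size are untouched.

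**What to change.** Amend the reporting sentence so that the estimate, interval and P-value for each secondary outcome come from one analysis.

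- **Positive skewed outcomes** (for example insulin, C-peptide, AUCins, triglycerides, testosterone and SHBG): analyse the log value by ANCOVA, with the log baseline as covariate where a baseline is measured. Report the ratio of geometric means, its 95% interval and the P-value from that model.
- **Outcomes kept on a rank test**, such as those that can be zero or negative and so cannot be logged: report the pairwise Hodges-Lehmann shift with its interval instead of a mean difference.

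The cost is about one sentence. The log transform and ANCOVA run in the named software, and no visit, measurement or sample size changes. The small downside is that effects are read as ratios and not in units. Trial status reports 114 of the planned 342 randomised at the end of December 2016, so at that stage the change could still be fixed before unblinding.

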## Discussion

Although we have confirmed that the combination of manual and low frequency EA can improve insulin sensitivity, hormone levels, and anxiety situation in patients with PCOS by the prospective study (ClinicalTrials.gov NCT02026323) [25], it had the limitation of being a single center study without comparison groups. There is still a lack of high-quality studies to determine the effect of acupuncture on insulin sensitivity in PCOS women and IR.

Based on the results of the prospective observational study (ClinicalTrials.gov NCT02026323) [25], we designed this randomized, double-blind, placebo-controlled, and multi-center study protocol to evaluate whether acupuncture treatment is more effective than metformin and sham acupuncture in improving the insulin sensitivity of PCOS and IR. The use of a larger sample size in a randomized setting, controlled by sham acupuncture and common medicine of insulin-sensitizing agents, will reduce the risk of type II error. Therefore, the results of this study may provide evidence for using acupuncture in future clinical practice in this area.

### Trial status

The study was registered at ClinicalTrials.gov on 24 June 2015. Recruitment was started on 11 November 2015 and is expected to end in March 2018. Recruitment is ongoing and 114 participants were randomized as of the end of December 2016. The final report will be available in 2018.
